### Sample and Setting

In mid-2023, we conducted a pilot study to evaluate feasibility and identify recruitment challenges before moving forward with the full RCT [27]. Between June 6, 2023, and July 20, 2023, 25 patients were recruited over 44 days at a single research site. Among these 25 patients, the mean VARS and Venham Behavioral Rating Scale scores before the procedure were 0.08 (SD = 0.28) for both scales, and during the procedure, the mean scores were 0.625 (SD = 1.35) and 0.667 (SD = 1.37), respectively. The variability in scores was higher at the time point with the higher average scores; therefore, we assumed a test with unequal variances. For the SAA outcome, data from a separate RCT conducted by our group were used [28]. This study measured changes in SAA before and during magnetic resonance imaging in children assigned to either a VR or a control condition. In that RCT, the mean difference in log-transformed SAA was 0.171 (SD = 1.05) in the control group and −0.096 (SD = 0.495) in the VR group. Because the expected difference in log SAA was smaller, this outcome guided our sample size calculations.

Therefore, to achieve 80% power to detect a mean difference of −0.096 (SD = 0.495) in log SAA using a 2-sided, 2-sample *t* test with unequal variances and a type-I error (α) of .05, a sample size of 364 participants (n=182 per group) was needed. Given the two primary outcomes, a Bonferroni correction was applied, reducing the α to .025. Based on an estimated 10% attrition rate from our pilot study, the final sample size was increased to 400 participants. Patients are currently being recruited for this study.

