#### Measures of Primary Outcomes

The first primary outcome will evaluate DFA using the VARS (Table 1) [25]. The VARS is an observation-based assessment by proxy for DFA and is among the most frequent anxiety scoring instruments for DFA [25]. The scale has been used as an anxiety rating scale in other studies that evaluated the efficacy of VR distraction in the management of DFA [32,33]. The anxiety scale consists of one item, with six defined anxiety levels that range from 0, representing the child being relaxed, smiling, and willing to cooperate, to 5, representing the child being out of contact with the reality of the threat. The highest score represents the highest anxiety level [25]. A high degree of reliability was observed for this scale, even by untrained observers [25,34]. A research assistant will indicate a score from 0 to 5 on the anxiety scale at T0 and T1 (Table 3).

The second primary outcome will assess the mean difference in SAA levels between T0 and T2, 10 minutes after the dental procedure. This enzyme is linked to both adrenaline and noradrenaline and is a validated and reliable specific biomarker of autonomic nervous system activity. It has been proposed as an alternative biomarker for anxiety, over salivary cortisol, as it reaches peak levels within 10 minutes after a stressful procedure compared to cortisol, which requires a 30-minute delay [16,35]. Enzyme sampling has been performed in previous studies to evaluate DFA in children undergoing dental procedures [35-37]. This enzyme is considered an accurate and noninvasive procedure for assessing anxiety-related events such as dental examination, cleaning, restoration, or extraction in children [26,35]. Alpha-amylase sampling has been performed in previous studies to evaluate DFA for children undergoing dental procedures [35,38]. Salivary samples will be collected using a sterile dental cotton swab from under the tongue and stored immediately within a sterile vial in a research-specific on-site freezer at −80 degrees Celsius. The research assistant will collect the samples and take them to the laboratory. Results will be entered in REDCap for analysis purposes after the study.

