### Statistical Analysis

The primary analyses for this study will follow an intent-to-treat approach, using randomization status as the independent variable, and the mean difference in anxiety (using the anxiety subscale of the Venham) during the dental procedure (T1) and the SAA mean difference between T0 and T2 as the primary outcomes. As there are two primary outcomes (anxiety subscale and SAA), a Bonferroni correction will be applied, and a significance level of *P*=.025 will be used to determine statistical significance of primary outcomes. An ANCOVA, adjusting for unequal variances and adjusted for the time of the procedure, age, and baseline (T0) anxiety or behavioral score, will be used to assess the mean difference in Venham anxiety score during the dental procedure (T1) between the experimental and the control groups. An ANCOVA, adjusted for time of procedure, neurodevelopmental diagnosis, age, and baseline SAA level (T0), will be used to assess the mean difference in SAA level between groups 10 minutes after the procedure (T2).

For the secondary outcomes analyses, parametric tests adjusted for procedural type, age, sex, and parental presence will be used. Comparisons of dichotomous variables, including the necessity of procedural retakes, the use of other nonpharmacological interventions, and the occurrence of side effects, will be assessed using the Cochran-Mantel-Haenszel test. We will also perform subgroup analyses by age group (6‐12 y vs 13‐17 y) and sex and gender (boys, girls, or other) using ANCOVA. Any side effects will be reported using the Medical Dictionary for Regulatory Activities terminology [42], and their proportions will be compared between groups.

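### The trial is sized on log-transformed SAA, but the primary SAA outcome and its ANCOVA are stated on the SAA level, so the 80% power does not belong to the test as written

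*Protocol article*

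**What the plan says.** Sizing, in Methods, Sample and Setting: from an earlier trial by the same group, "the mean difference in log-transformed SAA was 0.171 (SD = 1.05) in the control group"; the VR arm had −0.096 (SD 0.495). The article continues: "Because the expected difference in log SAA was smaller, this outcome guided our sample size calculations". It assumes a two-sided two-sample t test with unequal variances, 80% power and alpha reduced to .025 by Bonferroni. The result is 182 per group, 364 in all, raised to 400 for attrition.

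Outcome, in Measures of Primary Outcomes: "The second primary outcome will assess the mean difference in SAA levels between T0 and T2".

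Analysis, in Statistical Analysis: an ANCOVA adjusted for time of procedure, neurodevelopmental diagnosis, age and baseline SAA level "will be used to assess the mean difference in SAA level between groups 10 minutes after the procedure (T2".

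A log scale is mentioned only in Sample and Setting. It is absent from the outcome definition, the ANCOVA response and the baseline covariate. The allowance for unequal variances is attached to the Venham model and not to the SAA model.

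**The concern.** The sample size and the primary test are stated on two different scales. A difference in mean log SAA is a ratio of geometric means. A difference in mean SAA level is a difference of arithmetic means, and for a skewed marker the arithmetic mean depends on the spread of the logs as well as on their centre. So the two tests can differ in power and, in some circumstances, in what makes them reject.

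SAA is one of two primary outcomes, each tested at .025, so a significant SAA result alone could carry the trial's conclusion. The article reports 300 recruited as of November 2025, results expected in June 2026, and no blinding of staff. If the scale stays open until the data are seen, it can be chosen with the result in view.

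**Working it through.** **1. Reproduce the stated size on the log scale.** Inputs from Sample and Setting: changes of 0.171 (SD 1.05) and −0.096 (SD 0.495), two-sided alpha .025, power 80%, equal allocation.

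- Difference: 0.171 − (−0.096) = 0.267.
- Sum of variances: 1.05² + 0.495² = 1.1025 + 0.2450 = 1.3475.
- Normal approximation: n = 1.3475 × (2.241 + 0.842)² / 0.267² = 1.3475 × 9.505 / 0.0713 ≈ 180 per arm.
- Welch noncentral t: 182 per arm, power 80.1%.

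The stated 182 is reproduced, and it rests on log SAA. (The sentence in the article names −0.096 as the difference to detect, but the number comes from 0.267. That is a separate matter.)

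**2. Compare with the stated analysis.**

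| Element | Sizing | Primary analysis as written |
|---|---|---|
| Response | change in log SAA | SAA level at T2 |
| Baseline | inside the log change | SAA level at T0 |
| Variances | unequal | not mentioned for SAA |

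**3. Simulate both analyses.** Settings: 182 per arm; ANCOVA of T2 on arm and baseline; alpha .025; natural log and lognormal values assumed. The article does not give the SD of log SAA at baseline, so 0.6 to 1.2 is assumed. It also does not say how change relates to baseline. This matters because 1.05 and 0.495 are SDs of *change*, while the raw T2 mean depends on the variance of log SAA *at T2*. Two models are therefore shown for the planning SDs. The common SD is √(1.3475 / 2) = 0.82, with change independent of baseline.

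| Scenario | Raw-scale ANCOVA rejects | Log-scale ANCOVA rejects |
|---|---|---|
| Shift 0.267, equal change SDs (0.82) | 27–49% | about 80% |
| Shift 0.267, planning SDs, change independent of baseline | 87–99% | about 80% |
| Shift 0.267, planning SDs, T2 log variance equal to baseline in both arms | 39–95% | 80% or more |
| No log shift, planning SDs, change independent of baseline | 42–81% | 2–3% |
| No log shift, planning SDs, T2 log variance equal to baseline in both arms | 2–3% | 2–3% |

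Repeated runs move these figures by up to about three points. Within each row that includes a shift, raw-scale rejection falls as the baseline SD rises.

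**4. Why the two no-shift rows differ.** If change is independent of baseline, a larger change SD carries into T2. The SDs alone then give a ratio of arithmetic means of exp((1.1025 − 0.2450) / 2) = 1.54. If T2 has the same log variance as baseline, the change SDs affect only the T0–T2 correlation, r = 1 − SD² / (2 × baseline SD²), and the arithmetic means stay equal. For the control arm this gives:

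- baseline SD 0.6: r = 1 − 1.1025 / 0.72 = −0.53
- baseline SD 0.8: r = 1 − 1.1025 / 1.28 = 0.14
- baseline SD 1.0: r = 1 − 1.1025 / 2.00 = 0.45
- baseline SD 1.2: r = 1 − 1.1025 / 2.88 = 0.62

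The second model needs a negative correlation at the low end of the range but is unremarkable at the high end. The article does not settle which model is nearer the truth.

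**The case against.** **The text may not mean raw values.** The article uses SAA as the name of the marker, and Sample and Setting moves from changes in SAA to log-transformed SAA without remark. A condensed article can leave the transformation to an analysis plan, which is not shown. This stands in part: the article does not rule out a log analysis. But it does state the response, covariates, time point and alpha of this primary model, and it writes response and baseline as levels. An unseen plan that adds the log would not remove the conflict within the published text.

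**A reader might infer that the trial is underpowered for SAA.** The documents do not support that. With the planning SDs and change independent of baseline, raw-scale power is above 80%. It is well below 80% if the SDs are similar, and may be on either side if T2 variance equals baseline.

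**A reader might infer that the raw-scale test has a grossly inflated false-positive rate.** That is not shown either. The 42–81% figure requires change to be independent of baseline, and it drops to the nominal 2–3% when T2 variance is equal across arms. Even where it occurs, it reflects a real difference in arithmetic means. It is an error only with respect to the log shift on which the trial was sized. When arithmetic means were set equal with unequal SDs, raw-scale rejection was 4–5%.

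**The missing unequal-variance wording for SAA matters little.** This stands: under 1:1 allocation, robust standard errors moved the results by only about 3 points.

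**Conclusion.** The point holds as a mismatch of scale. The 80% power belongs to log SAA, and the primary SAA test is stated on the SAA level, so the power claim does not describe that test. Across the models examined, raw-scale power runs from 27% to 99%, and the article's figures do not show where in that range it lies. The log-scale ANCOVA keeps about 80% or more in all of them. The mismatch can be read directly from the text. The percentages rest on natural logs, lognormality, an assumed baseline log SD and an assumed relation between change and baseline. Rejection driven by unequal spread without any log shift is a possibility that the plan should close off, not a demonstrated error rate.

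**What to change.** State the primary SAA model as an ANCOVA on log(SAA) at T2 with log(SAA) at T0 as covariate, keeping the other listed covariates. Report a geometric mean ratio; if the log is natural, the planned effect is exp(−0.267) = 0.77, VR to control. Say log SAA in the outcome definition, and use the same scale in any SAA subgroup model. If the arithmetic mean is what is wanted, keep the raw level, say so, and restate the power with the baseline SD and T0–T2 correlation it needs. Carrying the unequal-variance allowance over to the SAA model would match the sizing, but it is optional.

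Cost: about one sentence in the analysis section and a matching phrase in the outcome definition, dated before the data are analysed. The log-scale option needs no new data and no change to the sample size.

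### The sample size is worked out on log-transformed SAA, but the primary SAA analysis is written for SAA level with no log, so read literally the stated 80% power does not describe the planned test

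*Protocol article*

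**What the plan says.** Under Sample and Setting, the planning figures for SAA come from an MRI trial by the same group: "the mean difference in log-transformed SAA was 0.171 (SD = 1.05) in the control group", and −0.096 (SD 0.495) in the VR group. The section adds: "Because the expected difference in log SAA was smaller, this outcome guided our sample size calculations". It arrives at 182 participants per group, 364 in all, for 80% power, and raises this to 400 for attrition.

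The log is not mentioned again. Objectives (Primary Outcomes) speaks of changes in mean SAA levels. Measures of Primary Outcomes states: "The second primary outcome will assess the mean difference in SAA levels between T0 and T2". Statistical Analysis names "the SAA mean difference between T0 and T2 as the primary outcomes" and describes an ANCOVA, with the baseline SAA level at T0 among its covariates, that "will be used to assess the mean difference in SAA level between groups 10 minutes after the procedure (T2").

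**The concern.** SAA is one of two primary outcomes, each tested at .025, and it is the one that fixed the sample size. If the analysis is run as written, on SAA level, no effect size, SD or power for that test appears in the article.

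The scale also changes the question. A log-scale comparison concerns geometric means. A raw-scale comparison concerns arithmetic means, and for skewed data these depend on spread as well as on the centre of the log distribution. The planning SDs of log change differ about twofold between arms, so the two analyses can disagree. If the scale stays open until the data are seen, the choice could decide whether this outcome is declared significant.

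**Working it through.** **Inputs from Sample and Setting.** Log change: control +0.171 (SD 1.05), VR −0.096 (SD 0.495); 182 per arm; two-sided alpha .025 after Bonferroni; 80% power.

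**Step 1: reproduce the plan's figure on the log scale.**
- Difference: 0.171 − (−0.096) = 0.267.
- SE = √[(1.05² + 0.495²)/182] = √[(1.1025 + 0.2450)/182] = 0.0860.
- 0.267 / 0.0860 = 3.10. The unequal-variance t test with a noncentral t gives power 80.1%, and 182 per arm is the smallest size that reaches 80%.
- Other readings do not give 182. A difference of 0.267 at alpha .05 needs 150 per arm. A difference of 0.096 with the two arm SDs needs 1,149 (alpha .05) or 1,392 (alpha .025).

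The 80% therefore belongs to a log-scale comparison. (The text names −0.096 as the difference and .05 as alpha. That is a separate wording problem.)

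**Step 2: what the raw scale compares.** Let SAA be lognormal, s₀ the SD of log SAA at baseline, and ρ the correlation of baseline with log change, the same in both arms. The variance of log SAA at T2 in an arm is s₀² + SD² + 2ρ·s₀·SD. With equal mean log change, the ratio of raw T2 means, control to VR, is

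exp[(1.05² − 0.495²)/2 + ρ·s₀·(1.05 − 0.495)].

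At ρ = 0 this is exp(0.4287) = 1.54. At s₀ = 1.2 and ρ = −0.5 it is exp(0.4287 − 0.3330) = 1.10. The spread effect is real under these assumptions, but its size depends on inputs that the article does not give.

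**Step 3: simulation.** ANCOVA of T2 on T0 and arm, 182 per arm, alpha .025, other covariates left out. The common SD is √[(1.05² + 0.495²)/2] = 0.82. Percentage of trials significant, raw / log (1,500 runs per setting; 800 in the last column):

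| s₀ | ρ | Equal mean log change, planning SDs | Planned means, planning SDs | Planned means, common SD 0.82 |
|---|---|---|---|---|
| 0.8 | 0 | 71 / 2 | 98 / 80 | 43 / 81 |
| 0.8 | −0.3 | 54 / 3 | 99 / 84 | 59 / 85 |
| 0.8 | −0.5 | 41 / 3 | >99 / 90 | 75 / 90 |
| 1.1 | 0 | 48 / 3 | 92 / 79 | 29 / 82 |
| 1.1 | −0.3 | 25 / 3 | 93 / 84 | 43 / 83 |
| 1.1 | −0.5 | 10 / 3 | 90 / 90 | 58 / 89 |

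Over s₀ from 0.6 to 1.2 and ρ from 0 to −0.5, the ranges are:
- equal mean log change, planning SDs: raw about 6-82%, log 2-3%;
- planned means, planning SDs: raw about 78-100%;
- planned means, common SD: raw about 22-81%, log 79-91%.

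Heteroscedasticity-robust (HC3) standard errors leave the spread-only rejections in the table almost unchanged, so the choice of standard error is not the cause.

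**Step 4: a setting in which the inflation vanishes.** The article gives SDs of change, not of T2. If each arm has ρ = −SD/(2s₀), the log T2 variance equals s₀² in both arms and the planning SDs of change still hold. With equal mean log change, the raw ANCOVA then rejects in 2.1%, 2.1% and 1.6% of trials at s₀ = 0.8, 1.0 and 1.2. Its power for the planned difference in that setting is 39-78%.

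**The case against.** The strongest reply is that no section says the analysis is untransformed. Sample and Setting is the only place that fixes a scale, and it fixes the log, so SAA level elsewhere may be shorthand. A full protocol or SAP that is not shown could state the transformation. This stands in part: the raw scale is the literal reading, not an explicit statement. But Statistical Analysis is specific. It names the model, response, baseline covariate, time point and alpha, and for the Venham score even an unequal-variance adjustment. Two stated parts of the same article do not match, which is more than an omitted detail.

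A reader might infer that the raw test will produce false positives through spread alone. The documents do not support that. The rejection rate depends on unstated inputs, can be as low as about 6% under a common correlation, and is about 2% when T2 log variances are equal. Where it is raised, the arithmetic means truly differ, so it is an error only with respect to the log effect the trial was sized on. The expected individual fold changes implied by the SDs alone, exp(1.05²/2) = 1.74 and exp(0.495²/2) = 1.13, do not settle it either: they are means of ratios, whereas the ANCOVA compares T2 means adjusted for T0.

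A reader might also infer that the trial is underpowered. That does not follow: with the planning SDs and a common correlation, raw-scale power is often above 80%. Nor do the documents give an SAA distribution from which to claim that a few extreme values would dominate.

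**Conclusion.** The point holds as a mismatch of scale. Read literally, the primary SAA test is not the test to which the 80% power belongs, and that power could lie well below or above 80% depending on quantities the article does not report. The clearest comparison is at equal spread: about 22-81% on the raw scale against 79-91% on the log scale for the same planned difference. The reproduction of 182 per arm rests on the article's own figures. The raw-scale ranges rest on lognormal SAA, natural logs, a baseline log SD of 0.6-1.2 and, except in Step 4, a common baseline-change correlation of 0 to −0.5. All of these are assumptions. The direction of the effect on the trial's result cannot be determined from the article.

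**What to change.** Before database lock, state in Objectives (Primary Outcomes), Measures of Primary Outcomes and Statistical Analysis that the second primary outcome is log-transformed SAA. Fit the ANCOVA to log SAA at T2 with log SAA at T0 as the baseline covariate and the other covariates as listed. Report the arm effect as a ratio of geometric means with its confidence interval, and show raw SAA descriptively only. If an existing SAP already says this, aligning the article's wording is enough.

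This needs no new data and no additional participants. The small cost is that the effect is expressed as a ratio instead of in enzyme units.

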**Methods:**

This randomized controlled trial follows a parallel design with two groups: a control group receiving standard care and an experimental group using VR. A sample size of 400 participants was calculated. Participants will be randomly assigned equally to each group. Recruitment will take place at the dental clinic of the Centre Hospitalier Universitaire Sainte-Justine, a tertiary- and quaternary-care center that primarily serves pediatric patients with SHCN. The two primary outcomes will include both observed and objective biomarker-based measures of anxiety. DFA will be evaluated using the Venham Anxiety Rating Scale as well as changes in mean levels of salivary alpha-amylase. Sociodemographic characteristics, parents’ and health care professionals’ satisfaction levels, participants’ pain intensity and behavior during the procedure, changes in heart rate, occurrence of side effects, procedure duration, and any deviations from normal procedural length will also be collected. Descriptive and comparative statistics will be conducted for demographic and clinical comparisons and will be used to present sociodemographic and clinical data, parents’ and health care professionals’ satisfaction levels, child satisfaction with the game, and procedural time.

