#### Secondary Outcomes

The secondary outcomes of this study are to compare the following indicators between the VR distraction and the standard intervention groups:

Parents’ (Multimedia Appendix 1) and health care professionals’ (Multimedia Appendix 2) satisfaction levelsChild satisfaction with the use of VR (Multimedia Appendix 1).Physiological parameters such as heart rate and oxygen saturationBehavior during the procedure (Table 2)Occurrence of side effectsLength of the dental procedureChild’s pain intensity (Multimedia Appendix 3)

**Table 2. T2:** The Venham Behavioral Rating Scale.

Rating	Definition
0	Total cooperation, best possible working conditions, and no crying or physical protest.
1	Mild or soft verbal protest, crying or quiet crying as a signal of discomfort, but does not obstruct progress. Appropriate behavior for the procedure, that is, slight start at injection, “ow” during drilling if hurting, and so on.
2	Protest more prominent. Both crying and hand signals. May move the head around making it hard to administer treatment. Protest is more distracting and troublesome. However, the child still complies with the request to cooperate.
3	Protest presents a real problem to the dentist. Complies with demands reluctantly, requiring extra effort by dentist. Body movement.
4	Protest disrupts procedure and requires that all of the dentist’s attention be directed toward the child’s behavior. Compliance was eventually achieved after considerable effort by the dentist, but without much actual physical restraint (may require holding the child’s hands or the like to start). More prominent body movement.
5	General protest, no compliance or cooperation. Physical restraint is required.

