#### Secondary Outcomes

The secondary outcomes include (1) parents’ and health care professionals’ satisfaction in both groups and children’s satisfaction in the VR intervention; (2) changes in physiological parameters, such as heart rate and oxygen saturation during and after the intervention compared to baseline; (3) behavior during the procedure; (4) occurrence of side effects (nausea, dizziness, and vomiting); (5) length of the procedure; and (6) the effectiveness of VR in reducing pain (Table 3).

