#### Measures of Secondary Outcomes

The secondary outcomes will be measured as follows:

Parents’ or legal guardians’ satisfaction with the intervention will be assessed using a Numerical Rating Scale (0‐10, where 0 is very dissatisfied and 10 is very satisfied) and according to the recommended question by the Pediatric Initiatives on Methods, Measurement and Pain Assessment in Clinical Trials: “Considering anxiety relief, side effects, and emotional recovery, how satisfied were you with the intervention used to manage anxiety experienced by your child?” [39] (Multimedia Appendix 1).Health care professionals’ satisfaction with the intervention will be assessed using a 6-question satisfaction questionnaire, with a range of scores from 1 to 4 (1=“Totally disagree,” 2=“Disagree,” 3=“Agree,” and 4=“Totally agree”; Multimedia Appendix 2).Child satisfaction with VR will be assessed using a 0‐10 numerical rating scale (where 0 is very dissatisfied and 10 is very satisfied; Multimedia Appendix 1).Physiological parameters (heart rate and oxygen saturation) will be measured using the COVIDIEN Nellcor pulse oxygen saturation meter, an approved and validated device.The patient’s behavior during the procedure will be assessed by proxy via a research assistant using the Venham Behavioral Rating Scale at T0 and T1 (Table 3) [25,40]. This 6-point scale assesses children’s behavior and provides information about patients with disruptive behavior. The scale points are based on objective, and readily observable behaviors and classify children’s behavior into 6 categories ranging from 0 (total cooperation) to 5 (general protest, no compliance, or cooperation). This scale has demonstrated good interrater reliability and has proven to be a valuable instrument for assessing children’s behavioral responses to dental procedures [40].Side effects will be collected in children in both groups from arrival on site until discharge, using a checklist of side effects commonly associated with VR, namely nausea, dizziness, and vomiting. Any of these side effects will be recorded along with the time they will occur.The length of the procedure in minutes will be measured and recorded for each participant and compared between the two groups.Pain will be assessed using the Face, Legs, Activity, Cry, and Consolability—Revised scale (FLACC-R) [41] (Multimedia Appendix 3). This questionnaire will serve to assess VR efficacy in reducing pain by comparing the mean pain level of both groups (experimental and control intervention) during the dental procedure (T1).

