### Study Proceedings Including Data Collection

Participants will be screened by a resident dentist or a research assistant via the appointment scheduling system for any dental procedure. Since DFA can arise from multiple procedures, such as simple cleaning to teeth extraction. A research assistant will review consent with participants and parents. Written consent by the parents or legal guardian—including the child’s assent (if possible)—will be obtained on arrival at the clinic, the day of the procedure, while completing the preprocedural questionnaire. After verifying that the participant meets all inclusion and exclusion criteria, the research assistant will log into REDCap only 10 minutes before the start of the intervention to minimize the risk of bias toward the intervention, obtain the group allocation, and then announce it to the participant. Because of the nature of VR, no blinding will be possible to staff, participants, parents, or legal guardians. Baseline data collection prior to the dental procedure, including a sociodemographic questionnaire, recording of physiological parameters, and SAA sampling, will take approximately 15 minutes to complete. The VR headset will be adjusted to the child’s size, and approximately 5 minutes will be allotted for the child to familiarize themselves with the room, equipment, and the game (VR or cartoon on TV or tablet) before the start of the procedure. The intervention will last the entire dental procedure, and its duration will be documented for each patient. DFA assessment by proxy using the VARS will be performed on site by the research assistant present. As per the clinic’s protocol, if a child becomes restless and uncooperative, they will be held by parents for the remainder of the procedure if it cannot be safely stopped at this time or if the procedure is considered an emergency. If the procedure can be safely stopped, rescheduling will be discussed with the parents, including the possible need for sedation. The involvement of parents will be recorded, as will any other distractions used during treatment, such as stickers, teddy bears, music, and others. The occurence of side effects and medications used will be recorded. The former will be transmitted to the ethics committee if they are serious or life-threatening. As VR has the potential to cause nausea, dizziness, and motion sickness, if participants experience any of these, they will be managed in accordance with the clinic’s protocols.

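### The covariate list for the secondary analyses leaves out the T0 value of the same measure, which gives up precision on heart rate, oxygen saturation, behaviour and pain at no saving

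*Protocol article*

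**What the plan says.** **Covariates.** The Statistical Analysis section sets one list for the secondary outcomes: "parametric tests adjusted for procedural type, age, sex, and parental presence will be used". The paragraph before it treats the primary outcomes differently. The Venham anxiety model is "adjusted for the time of the procedure, age, and baseline (T0) anxiety or behavioral score", and the salivary alpha-amylase model includes the T0 enzyme level.

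**Outcome definitions.** Under Objectives, the secondary aim is to "compare the following indicators between the VR distraction and the standard intervention groups". Heart rate and oxygen saturation stand in the list that follows, with no metric and no time point. Under Measures and Outcomes, the same outcome is "changes in physiological parameters, such as heart rate and oxygen saturation during and after the intervention compared to baseline". The Methods part of the abstract also speaks of change, for heart rate only: "changes in heart rate, occurrence of side effects, procedure duration". Pain on FLACC-R is assessed under Measures of Secondary Outcomes as a mean level at T1, compared between arms.

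**Data available.** Table 3 ticks physiological parameters at T0, T1 and T2, and VBRS and FLACC-R at T0 and T1. Study Proceedings confirms the T0 reading: "recording of physiological parameters, and SAA sampling, will take approximately 15 minutes to complete".

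**The concern.** Four secondary outcomes have a T0 measurement: heart rate, oxygen saturation, VBRS and FLACC-R. Followed as written, the secondary models do not use it as a covariate.

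- For heart rate and saturation, T0 enters only by subtraction. This fixes its coefficient at 1 whatever the true T0-to-T1 relation is.
- For FLACC-R, T0 does not enter the comparison at all.
- For VBRS, the article is unclear. The reference to a baseline anxiety or behavioural score belongs to the model for the Venham anxiety score, and may or may not have been meant to cover an analysis of behaviour.

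What is at stake is the width of the confidence intervals for these outcomes, and how far a chance T0 difference between arms shifts a particular estimate. The primary analyses and the sample size are not affected.

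**Working it through.** **Inputs**

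- Number per arm: 182 (Sample and Setting). This is the only figure taken from the plan, and it reproduces. A Welch t test with the difference 0.171 − (−0.096) = 0.267, SDs 1.05 and 0.495, and two-sided alpha .025 needs 182 per arm (power 80.1%).
- Effect on heart rate: 0.25 SD. Assumed.
- Two-sided alpha: .05 for a secondary outcome. Assumed.
- Correlation r between T0 and follow-up: not in the article. Range shown: 0.3 to 0.7.
- Equal SDs at T0 and follow-up, and no allowance for the covariates already listed. Assumed.

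**Step 1. Variance of the arm difference, relative to comparing follow-up levels**

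- Level without T0: 1
- Change score without T0: 2(1−r)
- T0-adjusted ANCOVA: 1−r²

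Change minus ANCOVA is 2(1−r) − (1−r²) = (1−r)², which is positive for every r below 1. Level minus ANCOVA is r², positive for every r other than 0. So the direction does not depend on the value of r chosen; only the size does.

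**Step 2. Power for heart rate, change score against T0-adjusted**

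SE = √(v × 2/182), where v is the relative variance. Power = Φ(0.25/SE − 1.96).

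| r | v, change | SE | Power | v, T0-adjusted | SE | Power |
|---|---|---|---|---|---|---|
| 0.3 | 1.40 | 0.124 | 52% | 0.91 | 0.100 | 71% |
| 0.5 | 1.00 | 0.105 | 66% | 0.75 | 0.091 | 79% |
| 0.7 | 0.60 | 0.081 | 87% | 0.51 | 0.075 | 92% |

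Put as sample size, the change score needs 1.40/0.91 = 1.54, 1.00/0.75 = 1.33 and 0.60/0.51 = 1.18 times as many children for the same precision.

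**Step 3. A chance T0 difference**

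The SE of the T0 difference between arms is √(2/182) = 0.105 SD, so differences up to 1.96 × 0.105 = 0.205 SD are within the usual 95% range. Take 0.2 SD and no treatment effect.

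- The expected follow-up difference is 0.2r. A level comparison (as for FLACC-R) therefore keeps +0.06, +0.10 and +0.14 SD at r = 0.3, 0.5 and 0.7.
- A change score gives 0.2r − 0.2 = −0.2(1−r), that is −0.14, −0.10 and −0.06 SD. The difference is over-corrected rather than left in.
- ANCOVA removes it in expectation.

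**Step 4. Level or change as the response**

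Once T0 is a covariate, taking the follow-up value or the change as response gives the same treatment effect and standard error; only the T0 coefficient shifts by 1. One addition to the model therefore also makes it immaterial that the Objectives list names no metric.

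**Step 5. VBRS and FLACC-R**

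Pilot behaviour scores before the procedure had mean 0.08 and SD 0.28 (Sample and Setting). On a 0 to 5 scale that is close to the floor, so T0 can explain little of the T1 score. The article gives no T0 figures for FLACC-R; a similar floor is likely but not shown.

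**The case against.** A reader might infer that the article contradicts itself, with a between-arm level under Objectives and a change from T0 under Measures and Outcomes. The text does not support this. The Objectives list names the parameters and gives no metric. A change from T0, compared between arms, satisfies that list, the later definition and the abstract together. The planned heart-rate analysis should therefore be read as a change score, and the fair contrast is change score against ANCOVA, as in Step 2.

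A reader might also infer bias, or that baseline differences stay in the heart-rate estimate. Neither follows. Randomisation keeps both level and change comparisons unbiased on average, and the change score over-corrects a chance difference instead of leaving it in. Nor should the point be strengthened by calling heart rate the only objective measure during the procedure: the same device reads oxygen saturation at T1.

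Three further objections carry weight. First, the list serves all secondary outcomes, and some, such as satisfaction and length of procedure, have no T0 value; a shared list would naturally omit it, and an unseen analysis plan may refine the models. Second, a change score for heart rate and a T1 comparison of pain are both legitimate in a randomised trial. Third, the effect size and r are assumed, and adjustment for age and sex may already recover part of the loss.

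These limit the severity but do not remove the point. The article does not stay silent on adjustment. It states a list, and it names a baseline term in both primary models directly above. Followed as written, that list gives a less precise result than data already in hand allow.

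**Conclusion.** The point holds as a low-severity matter of efficiency in secondary outcomes. Omitting T0 costs precision under either definition of the response.

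For heart rate as a change score, the illustrative loss of power runs from about 19 percentage points at r=0.3, through about 12 at r=0.5, to about 5 at r=0.7. This rests on an assumed 0.25 SD effect, 182 per arm, alpha .05, equal SDs and no credit for the other covariates. The same formulas apply to oxygen saturation, but the article offers nothing from which to judge its r. For VBRS and FLACC-R the gain is probably small.

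The primary conclusions, the sample size and the validity of the randomised comparison are untouched.

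**What to change.** In Statistical Analysis, extend the sentence on secondary outcomes: where the outcome was also measured at T0 (heart rate, oxygen saturation, VBRS, FLACC-R), the T0 value of that same measure is added to the listed covariates. In both Secondary Outcomes sections, state the physiological outcomes as the between-arm difference at T1 and at T2, adjusted for T0. If the baseline term in the Venham anxiety model was meant to cover the behaviour score as well, say so explicitly.

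The cost is two or three sentences. No extra children, visits or measurements are needed, because Table 3 already schedules the T0 values. The article reports 300 children recruited by November 2025 and expects results in June 2026, so the change should be dated and fixed before any between-arm comparison is run.
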